## HEALTH ECONOMIC EVALUATION

For the full trial, our proposed economic evaluation will be taken from an NHS and PSS perspective with a sensitivity analysis from a societal perspective. The outcome will be expressed as incremental cost per point improvement in the PHQ-9 clinical outcome, incremental cost per discontinuation of antidepressants, and incremental cost per quality adjusted life year (QALY) gained (cost utility analysis). Case note review at 6 and 12 months will augment the 6-monthly patient reports of health and social service resource use. All items will be costed using appropriate data (e.g. PSSRU, NHS reference costs), with informal care costed at minimum wage level. The primary analysis will be at 12 months. Personal costs will include patient and carer time off work, personal expenses, use of Internet, and travel. Itemised resource usage will be weighted by associated unit costs and aggregated over 12 months. Quality adjusted life years (QALYs) will be estimated by the area under the curve approach.

A generalised linear mix model will be used to estimate the differences in costs and QALYs (using both EQ-5D and SF-6D utilities), adjusting for baseline characteristics including socio-economic deprivation and internet use. Where appropriate we will estimate incremental cost-effectiveness ratios (ICERs). We will estimate mean values and 95% percentiles using non-parametric bootstrapping, and use these to estimate cost-effectiveness acceptability curves (CEACs). Major assumptions in the costing and quality of life analysis will be tested through sensitivity analyses. The decision analytic model developed during WS2 will be updated by the full trial evidence to extrapolate the cost-effectiveness beyond the trial period covering the potential risk of recurrence if the intervention proves to be effective in terms of improvements in QALYs up to 12 months. The health economics analysis will be published.

## PROCESS EVALUATION

The objective of the process evaluation in WS5 is to identify, characterise and explain factors likely to inform practitioner and patient behaviour change, to inform a robust implementation plan for the appropriate

discontinuation of antidepressants in clinical practice, through identifying and solving potential problems likely to inhibit the translation of the lessons of the REDUCE Trial into the everyday management of depression in primary care.

## Qualitative

The qualitative process study will use the same procedures as in the feasibility trial, interviewing 15-20 purposively sampled patients in each arm (or more if needed for saturation), and 15-20 practitioners in each arm, remotely or face to face, for up to 60 minutes. Interviews will be transcribed and themes identified through inductive analysis using constant comparison. We will interpret these in the light of Normalization Process Theory and use this to construct a taxonomy of factors affecting both the conduct of the trial, and its normalization potential beyond the trial. We anticipate where NPT does not characterise and explain data collected, we will identify constructs within the Consolidated Framework for Implementation Research (Damschroder 2009), and Michie's (2011) Theoretical Domains Framework. We will then be able to show how taxonomy components are explicable by reference to known mechanisms of embedding and integration in practice. The analysis will enable construction of an implementation framework of barriers and facilitators (patient and health system factors) that need to be taken into account in the design and delivery of the normalized intervention in practice, which we will publish.

Interviews will be semi-structured, focused on patient and practitioner experiences, but also informed by the 16 items developed to identify features of a complex intervention likely to be 'intervention killers' in everyday practice and operationalised in toolkit form at [www.normalizationprocess.org](http://www.normalizationprocess.org) (Murray 2010).

Individual patient interviews will explore in-depth user experiences of engaging with the intervention for a prolonged period, including:

- What worked well and what could have worked better
- Perspectives on mode of delivery and content, to gauge usability and understanding
- Burden of treatment from the patient's perspective

Individual practitioner interviews will explore their views on:

- Negotiating the decision to taper off treatment with their patients
- Their role as a GP/NP/PWP in terms of supporting/negotiating appropriateness of cessation
- Support needs in practice
- Ways to optimise implementation of cessation in routine practice, focusing on individual issues
- Follow-up monitoring of patients undergoing treatment tapering and cessation

The interviews will be transcribed and the data subject to inductive analysis using constant comparison to identify themes. We will interpret these in the light of Normalization Process Theory and construct a taxonomy of factors likely to affect the uptake and implementation of the intervention, and patient outcomes.

## Quantitative

We will examine the effects of baseline patient characteristics (e.g. demographics; prior internet experience, clinical characteristics) on engagement with the intervention and outcomes. Automatic data collection by LifeGuide will assess engagement (usage patterns), choice of self-management activities (e.g. cognitive exercises), progress and outcomes, and we will employ multi-level modelling to investigate how these relate to outcomes in mediation analyses.

## Psychological process measures

We will evaluate key psychological processes to find which elements are most important in predicting the success or otherwise of the intervention. These will include measures of patients' confidence, expectations and self-efficacy related to being able to reduce and stop their antidepressants. The questions will be taken from validated scales included in a psychometrically tested questionnaire developed by [name], a PhD student in our department at Southampton who is investigating the relationship between patients' attitudes towards antidepressants, confidence in being able to stop them, their perception of the views of important others (their doctor, family and friends), and intentions to stop, with the actual cessation rate over six months.

## ETHICAL CONSIDERATIONS

Patients with mental health problems like depression may be more sensitive than others to the demands of participation in research, but the effects of the problems in a primary care population are not so severe as to interfere with patients' capacity to understand the information provided or to give informed consent, provided patients with suicidal ideas, psychotic symptoms, and dementia are excluded. We have ensured the study aims are relevant to patients and the public through PPI input to the design, and their involvement will continue throughout to ensure that participation is voluntary, that easily understood patient information is provided, and fully informed consent obtained. Confidentiality and freedom to drop out at any time (see below) will be ensured.

In obtaining and documenting informed consent, the researcher will comply with applicable regulatory requirements and adhere to the principles of Good Clinical Practice (GCP). Discussion of objectives, risks and inconveniences of the study and the conditions under which it is to be conducted will be provided to the participant by appropriately delegated staff with knowledge in obtaining informed consent and with reference to the patient information leaflet. This information will emphasise that participation in the trial is voluntary and that the participant may withdraw from the trial at any time and for any reason. The participant will be given the opportunity to ask any questions that may arise and provided with the opportunity to discuss the study with family members, friend or an independent healthcare professional outside of the research team and time to consider the information prior to agreeing to participate.

Independent peer review through the NIHR PGfAR panel has ensured scientific quality and rigor. Ethics Committee and HRA approvals will be obtained prior to commencement of work with patients and health professionals, and any subsequent issues will be addressed with the REC or HRA offices as necessary.

## PROGRAMME STEERING COMMITTEE

A Programme Steering Committee (PSC) is in place, chaired by an academic GP, and including a senior statistician, an academic psychologist, and two PPI members. The PSC will work with the Independent Data Monitoring Committee (IDMC) and be kept informed by the CI, PI, or Programme Manager. If an extension to the study is asked for, it would be the responsibility of the PSC to look in detail as to why this was needed and give an opinion which would inform the funder (NIHR) and the sponsor (University of Southampton).

## INDEPENDENT DATA MONITORING COMMITTEE

In addition to the PSC, an IDMC has been set up to oversee trial conduct, chaired by an academic psychiatrist, and including an academic GP, and a senior statistician. The IDMC is tasked with looking at data, statistical and ethical aspects. Serious adverse events will be reported to the IDMC (see below) who will advise about continuation and whether interim analyses are needed. If there is a need to ask for an interim analysis of findings the IDMC will look at them but it would be the PSC who would make the ultimate decision about whether the trial might be stopped, extended or have a substantial change to its protocol.

## SAFETY OF PARTICIPANTS IN THE TRIAL

We have been advised by the Medicines and Healthcare Products Regulatory Authority (MHRA) that the study is not a clinical trial of an investigational medicinal product (CTIMP), and so a Clinical Trials Authorisation (CTA) is not required. Therefore the study team will not be bound by the MHRA CTIMP regulations on alerting the sponsor and ethics committee within specific timescales of any adverse events, or potential adverse effects of the intervention or trial procedures, which are reported by patients or practitioners participating in the trial.

However, the safety of patients in the trial remains our paramount consideration and the trial coordinator will ensure that any adverse events reported by patients or practitioners will be brought to the attention of the Programme Manager at [[contact]](mailto:[contact]) ([contact]) as quickly as possible. It will then be for immediate discussion with the Chief Investigator (CI) or in the absence of the CI, one of the Principal Investigators (PIs). The CI or PI will

decide whether or not to inform the Sponsor, the Ethics Committee, PSC and/or IDMC. The report will include the event, when the information was reported, assessment of seriousness and likely relationship to participation in the trial.

All serious adverse events (SAEs) will be reported to the Programme Manager at [[contact]](mailto:[contact]) ([contact]) and sponsor- The University of Southampton within 24 hours of the local site becoming aware of the event. We will use the Southampton CTU's SAE Non-CTIMP Form, which asks for the nature of the event, date of onset, severity, corrective therapies given, outcome, causality (i.e. unrelated, unlikely, possible, probably, definitely) and expectedness. The Chief Investigator will assign the causality and expectedness of the event and the term should be in accordance with the latest version of MedDRA and grades given in accordance with the NCI CTCAE v4.03. Additional information will be provided as soon as possible if the event has not resolved at the time of reporting.

The Chief Investigator or Programme Manager will notify the REC of related and unexpected SAEs occurring during the study according to the following timelines; fatal and life-threatening within 7 days of notification and non-life threatening within 15 days.

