### 6.4.1 Expected Adverse Events:

|                                           |                                                                                                                                                                                                           |
|-------------------------------------------|-----------------------------------------------------------------------------------------------------------------------------------------------------------------------------------------------------------|
| Mild antidepressant withdrawal symptoms   | Likely to occur in around half of patients reducing and stopping their antidepressants. If mild enough to be tolerated by patient, and short-lived (up to two weeks), these do not need reporting as AEs. |
| Moderate to severe withdrawal symptoms    | If severe or prolonged withdrawal symptoms occur, requiring restarting of antidepressant, please report as related and expected AE.                                                                       |
| Relapse of depression or anxiety disorder | May occur in 10-20% of patients over the one year follow-up, requiring restarting of antidepressant. Please report as related and expected AE.                                                            |

The nature or severity of should be considered when making the assessment of expectedness. If these factors are not consistent with the current information available then the AE should be recorded as 'unexpected'.

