## Intervention arm

The practitioner intervention (called 'ADvisor for Health Professionals' as it gives advice about AntiDepressants) includes Internet modules on: Why reduce; Broaching the subject; When to start tapering; Reduction schedules for individual antidepressants; Dealing with withdrawal symptoms; Dealing with relapse; ADvisor for patients (a summary); and printable pages on antidepressant reduction regimes and sections of ADvisor for patients to recommend patients consult.

The patient intervention (called 'ADvisor for Patients') includes Internet modules on: Reducing and stopping (introduction to website); How to reduce antidepressants; Thinking about antidepressants (their effects and why lifelong treatment may not be necessary); Dealing with withdrawal symptoms; I'm worried about stopping; Keeping well; Thinking about what you value in life; and Moving forward.

In the intervention arm practices, the GPs/NPs will be given access to the on-line ADvisor for practitioners, and induction to the study, which will be either practice-based or on-line. They will receive an introduction to ADvisor, and education on best practice in the supervision of antidepressant tapering and cessation, focussing on the differences between withdrawal symptoms and relapse, and the management of withdrawal symptoms.

The number and timing of subsequent GP/NP consultations during tapering and following drug cessation will be left to the participating GPs/NPs to agree with the patients on an individual basis.

In addition to the ADvisor Internet modules and GP/NP consultations, the following telephone support will be provided to patients in the intervention arm by a trained psychological practitioner (PP):

- Call 1 (0-2 weeks), for 30 minutes: to check the patient's understanding of the ADvisor intervention and encourage confidence in going through the tapering and cessation process
- Call 2 (4-6 weeks), for 15 minutes: to ask the patient how tapering is going and whether they are following the schedule, and where necessary, to advise the patient to discuss any issues with tapering with their GP
- Call 3 (timing agreed with patient), for 15 minutes: to ask the patient about any residual withdrawal symptoms and go over techniques to help with relapse prevention.

A sample of 10-20 telephone calls per practitioner will be audio-recorded in the first three months, and again halfway through the trial, to check for fidelity against the telephone support guise.

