## Costs

A societal perspective will be taken for the health economics analysis. Bespoke questionnaires, developed in light of the WS1 systematic review and WS2 qualitative interviews, and modified in light of the experience of using them in WS4, will be used to collect data on health and social service resource use; personal out of pocket spending; and time off work.

In addition, a review of patients' computerised GP records will be conducted by practice staff to extract any additional health service usage including medication, primary care consultations, outpatient appointments, A&E attendances, and hospital admissions. All items will be costed using appropriate data (e.g. British National Formulary, Personal Social Service Research Unit (PSSRU) and NHS reference costs), with informal care costed at minimum wage level.

The resource use questionnaire will be administered face to face with patients at baseline, 6 and 12 months, asking them to look back over the previous 6 months at each point. The case note review will be done by general practice staff looking back over the previous six months from the six-month follow-up point, and again from the end of the 12 months follow-up.

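### Adverse events are captured only when someone reports them, contact with practitioners differs by arm, and admissions already collected in both arms are not linked to SAE reporting

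*Combined protocol and SAP*

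**What the plan says.** **Route of entry.** The protocol section Safety of Participants in the Trial states that "any adverse events reported by patients or practitioners will be brought to the attention of the Programme Manager". The Chief Investigator or a Principal Investigator then decides whether the sponsor, ethics committee, steering committee or IDMC is told. SAEs must be reported "within 24 hours of the local site becoming aware of the event". No section says how a site is to become aware.

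**Scheduled contacts.** The Consent and data collection summary lists every measure at baseline, 3, 6, 9 and 12 months. It has no AE or SAE row.

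**Contact by arm.** The Intervention arm section gives intervention patients three telephone calls. The purpose of the third is "to ask the patient about any residual withdrawal symptoms and go over techniques to help with relapse prevention". Practitioners in that arm are also educated on separating withdrawal from relapse. The Control arm section provides a flagged record and a review appointment, with no calls and no such training.

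**Admissions.** Under Costs, practice staff review GP records to "extract any additional health service usage including medication, primary care consultations, outpatient appointments, A&E attendances, and hospital admissions", covering the six months before the 6-month point and again up to 12 months. A patient service-use questionnaire is given at baseline, 6 and 12 months. Neither source is restricted by arm.

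**Use of the safety data.** SAP section 4.7 plans a listing of SAEs, with a summary table if required. The protocol sends SAEs to the IDMC, which advises on continuation.

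**The concern.** When events are counted only if someone volunteers them, the count depends on the true rate and on how often, and to whom, the patient has occasion to speak. Here that second factor differs by arm by design. It also depends on how a practitioner classifies what is described. The protocol's list of expected events exempts mild, short-lived withdrawal from reporting, and says of it: "Likely to occur in around half of patients reducing and stopping their antidepressants". More serious withdrawal is treated differently: "If severe or prolonged withdrawal symptoms occur, requiring restarting of antidepressant, please report as related and expected AE". Deciding which side of that line a patient falls on is a judgement that only one arm's practitioners are trained to make.

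The programme aim includes safety. A difference between arms in the SAE listing, or the absence of one, would be hard to interpret if the listing rests on unsolicited reports. The IDMC would be advising on the same material.

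**Working it through.** This is mainly a comparison of sections. Arithmetic enters only at steps 3 and 5.

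1. **Is there a solicited AE question?** The rows of the data collection summary are: consent to contact, eligibility, consent, sociodemographics and history, PHQ-9, GAD-7, suicidal ideas, discontinuation, EQ-5D/SF-12, WEMWBS, DESS, ASEC/CSFQ-C, MISS-29, PEI, the questionnaires on services, antidepressant use, sickness absence and beliefs, and collective efficacy. None is an AE or SAE item. The safety text at the front of the protocol, the later safety section, the IDMC section and SAP 4.7 do not tell anyone to ask.

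2. **Which harms are nonetheless solicited equally?**

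| Measure | Follow-up times | Arm restriction |
|---|---|---|
| PHQ-9, GAD-7, suicidal ideas | 3, 6, 9, 12 months | none |
| DESS withdrawal symptoms | 3, 6 months | none |
| Service and antidepressant use | 6, 12 months | none |

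The scales therefore do not share the problem. No section turns a follow-up score into an AE report, DESS stops at 6 months, and none of the symptom scales records an admission.

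3. **How much extra contact is there?** Calls of 30 + 15 + 15 = 60 minutes agree with the one hour over three calls given in the protocol's WS3 section. Call 1 concerns understanding and confidence, and call 2 the progress of tapering. Only call 3, 15 of the 60 minutes, names withdrawal or relapse. No section says that psychological practitioners log AEs, so the calls are an opportunity to report and not a documented reporting route.

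4. **Do admissions reach SAE reporting?** The Definitions section makes hospitalisation an SAE, apart from admissions for pre-existing conditions that have not worsened. The record review collects admissions in both arms. The stated use is costing (Costs; Health Economic Evaluation). The Data collection section mentions record extraction without giving a purpose. No section passes the admissions to the SAE process.

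5. **Can the effect be sized?** Recorded events per arm = n × true risk × detection probability. With equal n and equal true risk, the ratio of recorded events is simply d(intervention) / d(control). The documents give neither probability. Inputs: n = 360 / 2 = 180 per arm; true relapse risk 20%, the upper end of the protocol's 10-20%; detection ASSUMED.

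   - 80% v 80%: 180 × 0.20 × 0.80 = 28.8 in each arm, ratio 1.00
   - 80% v 70%: 28.8 v 25.2, ratio 1.14
   - 80% v 60%: 28.8 v 21.6, ratio 1.33
   - 70% v 80% (direction reversed): 25.2 v 28.8, ratio 0.88

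   At 10% risk the counts halve and the ratios are unchanged. The output repeats the assumption, so it shows the mechanism and not the size.

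**The case against.** The strongest reply is that the foreseeable harms of stopping an antidepressant are worsening depression, anxiety, suicidal ideas and withdrawal symptoms. All are asked about on the same schedule in both arms, and PHQ-9, GAD-7, DESS and discontinuation are SAP endpoints. The SAP lists SAEs and plans no between-arm test of AEs. Nothing shows that three short calls change the detection of deaths or admissions. All of this stands, and it limits the point to reported events. It does not answer the absence of any solicited event item or of any link from admissions to SAEs.

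A reader might infer more in four ways that the documents do not support.

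- *Harms will be detected unequally, to the intervention's disadvantage.* No detection rates are given. Extra contact could raise reports, while training in telling withdrawal from relapse could lower the number labelled as relapse.
- *A relapse in a patient still on treatment is not reportable.* The entry for relapse reads: "May occur in 10-20% of patients over the one year follow-up, requiring restarting of antidepressant. Please report as related and expected AE". That list is introduced as the basis for judging expectedness. The Definitions section makes any untoward medical occurrence an AE, and events that do not match the list are to be recorded as unexpected.
- *A control admission would be missed altogether.* The questionnaire and the record review may both bring it into the trial's data. The gap is that it may never become an SAE report.
- *The distortion could be near twofold.* Assuming 90% v 50% detection gives 32.4 v 18.0 relapses and a ratio of 1.8, but this only returns 0.90 / 0.50. It also concerns mostly non-serious events that the SAP does not list.

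**Conclusion.** The concern holds in a limited form. AEs and SAEs enter the trial only when reported, and no scheduled contact solicits them. Contact and practitioner training differ by arm, and admissions collected in both arms have no stated route into the SAE process. Reported AE and SAE counts, including the SAP listing and the IDMC's material, may therefore be incomplete and may not be comparable between arms. The direction is unknown and no size can be given from the documents.

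The primary analysis of PHQ-9 and the other scale-based comparisons are not affected by this. The conclusion assumes that no unpublished working instruction tells researchers to ask about events or to pass admissions on. If one exists, it should be cited in the protocol.

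**What to change.** 1. **Link admissions to SAE reporting.** State that admissions found in the 6- and 12-month service-use questionnaire and in the record review are processed as SAEs in both arms, subject to the protocol's own exclusion for pre-existing conditions. Reconcile the SAE listing against them before the final analysis. This needs no new patient contact and remains possible even if visits can no longer be changed. Two details need settling. The questionnaire's items are not in the documents, so confirm that they cover admissions. The Data collection and Blinding sections place record extraction at the end of the study, in which case it can complete the listing but comes too late to inform the IDMC during the trial.
2. **Ask the same question in both arms.** Add one short AE/SAE item at the existing 3, 6, 9 and 12 month contacts.
3. **Record the source of each report** (scheduled item, questionnaire, record review, practitioner, psychological practitioner call), and base any between-arm comparison on sources common to both arms. A call as source reveals allocation, so this field should be kept from the blinded follow-up researchers.

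The cost is a protocol amendment, slightly longer questionnaires, more events to process, and a sentence in SAP 4.7 describing the reconciliation.
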